### Data collection

The study data will be collected at the time points summarised in table 3.

**Table 3 T3:** CYCLIST summary of time points of assessments

	Baseline	Day 3	Day 7	Day 10	ICU discharge	1 week post ICU discharge*	3, 6 months’ post ICU-admission
Severity of illness							
APACHE III	✓						
SOFA	✓	✓	✓	✓	✓		
Muscle morphology							
Quadriceps ultrasonography	✓	✓	✓	✓		✓	
Strength measures							
MRC sum score					✓	✓	
Handgrip dynamometry					✓	✓	
Physical function measures							
ICU mobility scale					✓		
FSS-ICU					✓		
Functional milestones	✓	✓	✓	✓	✓	✓	
6-MWT						✓	
Cognition							
CAM-ICU	✓	✓	✓	✓	✓		
Quality of life							
EQ-5D-5L				✓			✓
Acceptability of intervention							
Participant acceptability				✓†			
Patient outcomes							
ICU length of stay					✓		
Hospital length of stay						✓‡	
Acute discharge destination						✓‡	
Mortality					✓	✓‡	✓

*1-week post-ICU discharge or at acute hospital discharge if sooner.

†At completion of in-bed cycle ergometry sessions.

‡Measured at acute hospital discharge.

6-MWT, 6 min walk test; APACHE, Acute Physiology and Chronic Health Evaluation; CAM-ICU, Confusion Assessment Method for the Intensive Care Unit; CYCLIST, Critical Care Cycling Study; EQ-5D-5L, EuroQol Five Dimensions questionnaire Five Levels scale.; FSS-ICU, Functional Status Score for the Intensive Care Unit; ICU, intensive care unit; MRC, Medical Research Council; SOFA, Sequential Organ Failure Assessment score.

The management of study data will be dependent on the type of data collected. Baseline data will be entered directly into REDCap-designed digital clinical trial workflow management software.^13^ Ultrasound results will be uploaded onto the secure hospital-based AGFA IMPAX 6.5.3.1005 Medical Image Viewer application. In-bed cycling session data, physical assessment measures, acceptability of in-bed cycling intervention and quality of life questionnaires will be recorded initially onto research data sheets. All information recorded on data sheets will be subsequently entered into the REDCap application.

Assessments of muscle size will be assessed by ultrasound and performed by registered postgraduate trained sonographers with expertise in musculoskeletal sonography. Sonographers will be blinded to patient treatment group allocation and will be responsible for analysing and scoring all ultrasound images. The study sonographers were involved in the development and standardisation of the ultrasound procedure prior to the commencement of the study.

Assessment of muscle strength and function will be completed by cardiorespiratory physiotherapy assessors with a minimum of 3 years’ experience at participants’ ICU discharge and 7 days post-ICU discharge. These physiotherapists will be blinded to group allocation. The same physiotherapists will also assess 6 min walk test distance 7 days following ICU discharge. The study physiotherapists were trained in the standardised assessment of the study outcome measures prior to the commencement of the study.

A physiotherapist not involved in blinded outcome assessment will be responsible for conducting the in-bed cycling sessions, and the remaining ‘usual care’ physiotherapy will be completed by hospital department physiotherapists not involved in the study. Additionally, the primary statistician will be blinded to treatment group allocation.

To minimise the chances of unintentional unblinding, at the beginning of each assessment the blinded assessors will clearly state that they wish to complete the assessment process without knowing which group the patient was allocated to. If any blinded assessors were to become unblinded to group allocation for any patient (eg, through inadvertent revelation by a patient being assessed or unanticipated exposure to a patient taking part in an in-bed cycling session), they have been instructed to report this to the intervention coordinator ([name]) who will also record when this occurred.

### Analysis

Data will be analysed and reported using intention-to-treat principles (primary analysis). A per-protocol analysis will be conducted to assist in determining the efficacy of the in-bed cycling protocol if variation from the planned protocol occurs for a substantial proportion of patients. The per-protocol analysis will include only patients who adhered to the protocol and received at least 80% of training sessions (minimum of four sessions).

Descriptive statistics and generalised linear mixed models (that can adjust for baseline status) will be used to examine the effect of group allocation (intervention vs usual care) on the primary and secondary outcomes.^18^ As this is a randomised trial, we do not plan to adjust for potential confounders (eg, age, gender, comorbidities), but will compare the characteristics of the sample by treatment group and may adjust if a potential confounder differs greatly between groups.

If blinded sonographers are unable to complete an ultrasound measurement at designated time points, then the scan will be performed within a day (±1 day) of the designated time point. A subsequent sensitivity analysis will be conducted to determine if there is a difference by measurement timing. If the primary outcome cannot be collected by a sonographer within the specified time frame, a physiotherapist experienced in musculoskeletal ultrasound will measure thigh muscle size. The measurement will be from the most anterior aspect of rectus femoris to the anterior surface of the femur. This will assist in the imputation of the missing primary outcome data. Statistical analysis of available data will be used for the primary analysis when data are completely missing. Multiple imputation will be conducted if more than 20% of outcome data are missing. Additional planned secondary analyses are listed in box 2. The principal investigators will determine if study protocol modifications are required and any modifications to the existing protocol will be declared.Box 2Planned secondary analysesMuscle wasting at baseline, day 3, day 7 and 1 week post-ICU dischargeMuscle wasting adjusted for number of failing vital organs*Muscle wasting adjusted for severity of illness on admission to ICU†Muscle wasting adjusted for the number of days prior to a patient commencing active activityMuscle wasting adjusted for the patients’ cumulative fluid balance on the day of the ultrasound scanRelationship between muscle wasting and participants’ nutritional intake while in ICURelationship between sedative and paralytic medications and muscle wastingCost comparison of hospitalisation for both the intervention and usual care groups‡Hospital readmissions after acute hospital discharge over a 2-year time period§Mortality¶Utilising:*Sequential Organ Failure Assessment (SOFA).†APACHE III (Acute Physiology and Chronic Health Evaluation) data.‡Health service utilisation data.§Queensland Hospital Admitted Patient Data Collection (QHAPDC).¶Queensland Health Statistical Services Branch.ICU, intensive care unit.

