### Participants

The study aims to recruit 68 participants. Adult patients expected to require at least 48 hours of mechanical ventilation will be recruited, with the inclusion and exclusion criteria listed in table 1. Criteria to guide when to discontinue or not deliver an intervention are listed in box 1. Participants can be recruited into the study and baseline sonography measures performed if a patient does not currently meet the in-bed cycling safety criteria in box 1 (but are considered by their treating clinical team to be likely to meet the criteria within their stay in ICU).

**Table 1 T1:** Inclusion and exclusion criteria

Inclusion	Exclusion
Expected to require more than 48 hours of invasive mechanical ventilation	Pre-existing condition that is likely to impair mobility/mobility assessment (ie, significant neurological, musculoskeletal, cognitive or mental health disorder)
Able to provide consent or have a family member consent on their behalf	Neuromuscular disorder or acute primary brain lesion (ie, traumatic brain injury, intracranial haemorrhage, stroke or hypoxic brain injury)
Enrolled into the study within 96 hours of ICU admission	Injuries precluding cycle ergometry (ie, spinal/pelvic/lower limb orthopaedic injuries/open abdominal wound)
Expected to remain in ICU for more than 48 hours following study enrolment	Obesity >135 kg (MOTOmed Letto 2 maximum rated weight capacity)
	Uncontrolled seizures or status epilepticus
	Dire prognosis (ie, unlikely to survive the current admission)
	Pregnancy
	Children and/or young people (ie, <18 years)

ICU, intensive care unit.

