### Study intervention

All study patients will receive usual physiotherapy interventions while in intensive care. Physiotherapy interventions will include (but are not limited to): respiratory physiotherapy, physical rehabilitation exercise interventions including sitting on the edge of the bed, sit to stand transfers, sitting out of bed and walking. Usual care physiotherapy interventions will be prioritised over the in-bed cycling intervention. Safety guidelines (see box 1) will be used to determine if the intervention group patients are able to complete an additional daily 30 min progressive lower limb in-bed cycling using a bedside cycle ergometer (MOTOmed Letto 2). The lead physiotherapist ([name]) who has over 10 years of experience in rehabilitative exercise with patients with critical illness will primarily conduct the majority of in-bed cycling sessions. He has been trained by industry cycle ergometry representatives and has over 5 years of experience conducting in-bed cycling sessions with patients with critical illness. Experienced ICU physiotherapists trained in conducting in-bed cycling sessions may conduct the in-bed cycling sessions if the lead physiotherapist is unavailable. During the in-bed cycling exercise interventions, the patients’ vital signs will be monitored. If the intervention group patients are in a state of low arousal or sedated, they will cycle continuously and passively at the default passive speed of the cycle ergometer (20 revolutions per minute) for 30 min. When the participant is following commands, the clinician will verbally encourage the patient to complete in-bed cycling sessions actively for a duration of 30 min. Once the patient can cycle actively, the resistance applied by the cycle ergometer will be adjusted to facilitate patient intensity between 3 and 5 using the visual Borg scale rate of perceived exertion (category ratio 10),^14^ within the specified safety guidelines. An exercise intensity of 3–5 on the Borg rate of perceived exertion scale has been shown to be safe and feasible with patients with critical illness.^15^ This will enable the patient to cycle in-bed either passively or actively with assistance from the cycle ergometer. If a patient unexpectedly commences active cycling, the additional active in-bed cycling safety criteria will become relevant. If the patients are deemed unsuitable to continue active in-bed cycling, they will be asked to resume passive cycling. If the patient continues to actively cycle, the session will be ceased. The in-bed cycling sessions will continue until the patient completes a minimum of five in-bed cycling sessions, unless the patient is discharged from hospital prior to completing five sessions. The intervention will continue in the acute hospital ward if the patient is discharged from ICU prior to completing five in-bed cycling sessions. While the patient remains in ICU, in-bed cycling sessions will continue (up to 7 days/week), up to 28 days post-ICU admission. This frequency is congruent with usual physiotherapy services that can provide rehabilitative exercise interventions to ICU patients up to 7 days/week. Patients randomised to the usual care arm do not routinely complete in-bed cycling sessions during their hospitalisation. Any deviations from the planned protocol will be recorded to enable appropriate intervention description and, if indicated, a per-protocol analysis (in addition to the primary intention-to-treat analysis).

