### Outcomes

Table 2 provides a summary of the outcome measures. The primary outcome is the percentage of change in rectus femoris CSA measured at baseline (within 24 hours of study enrolment) and day 10 (post study enrolment), measured by a blinded assessor. The participants will be assessed to examine whether there is a between-group difference in the amount of rectus femoris CSA atrophy. The authors anticipate that less rectus femoris CSA atrophy will be observed among the in-bed cycling group. Day 10 post study enrolment has been chosen as the primary endpoint to enable comparison with previously published data on acute skeletal muscle wasting in patients with critical illness and consistent with this previously reported time frame of observed muscle wasting.^1^ Secondary outcome measures in the CYCLIST (Critical Care Cycling Study) are muscle strength, physical function, cognition, quality of life and acceptability of intervention.

**Table 2 T2:** Descriptions of outcome measures for CYCLIST RCT

Assessment component	Outcome measure	Description
Muscle morphology	Ultrasound	RF CSA, AP thickness of RF and VI. Measured in triplicate on right anterior thigh one-third distance from superior patella to ASIS. Patient positioned in supine, 30º head elevation^27^
Muscle strength	MRC sum score	Standardised sum of 12 MMTs, 3 MMTs per limb Score ≤48 indicative of ICU-acquired weakness^28^
	Handgrip strength dynamometry	Triplicate bilateral measurement using a Jamar Digital Dynamometer (Lafayette) with seated patient^29^
Physical function	ICU Mobility Scale	Best level of function achieved in ICU using an 11-point ordinal scale^30^
	FSS-ICU	Patients’ function measured an 8-point ordinal scale^31 32^
	Functional milestones	Time to achieve functional milestones: sit out of bed, time to stand, mobilise with assistance and mobilise independently
	6 min walk test	Submaximal endurance test of distance walked by a patient in 6 min^33^
Cognition	CAM-ICU	Incidence and recorded episodes of acute delirium^34^
Quality of life	EQ-5D-5L	EQ-5D-5L^35^
Intervention acceptability	Customised questionnaires	Questionnaire about the acceptability of the in-bed cycling intervention

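### The per-protocol set filters only the cycling arm, on sessions received at any time, so its day-10 comparison is open to selection bias and can credit sessions given after the outcome

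*Protocol article*

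**What the plan says.** All references are to the protocol article.

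- **Primary analysis (Analysis):** "Data will be analysed and reported using intention-to-treat principles (primary analysis".
- **Per-protocol rule (Analysis):** "The per-protocol analysis will include only patients who adhered to the protocol and received at least 80% of training sessions (minimum of four sessions".
- **Purpose and trigger (Analysis):** the per-protocol analysis is conditional, and is meant "to assist in determining the efficacy of the in-bed cycling protocol if variation from the planned protocol occurs for a substantial proportion of patients".
- **Primary endpoint (Outcomes):** percentage change in rectus femoris cross-sectional area between baseline and "day 10 (post study enrolment), measured by a blinded assessor".
- **Session period (Study intervention):** "The in-bed cycling sessions will continue until the patient completes a minimum of five in-bed cycling sessions", unless hospital discharge comes first. In ICU, "in-bed cycling sessions will continue (up to 7 days/week), up to 28 days post-ICU admission". After ICU, "The intervention will continue in the acute hospital ward if the patient is discharged from ICU prior to completing five in-bed cycling sessions".
- **Who can be cycled (Participants and Box 1):** sessions are withheld from patients judged unstable or outside listed physiological limits. Patients may be enrolled before they meet those criteria.
- **Usual care (Study intervention and Discussion):** these patients do not routinely cycle, and the amount of physiotherapy they receive is not recorded prospectively.

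**The concern.** The rule has three features that work badly together.

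1. **Membership is decided after randomisation.** Reaching four sessions requires being stable enough, often enough, and staying long enough. These aspects of the illness course may also influence muscle loss. Box 2 plans analyses of muscle wasting adjusted for organ failure and for severity on admission, so the investigators themselves treat severity as relevant.
2. **The filter acts on one arm.** No usual-care patient has cycling sessions to count, and no substitute criterion is given. Because usual-care physiotherapy is not recorded, a matching dose rule could not be built afterwards.
3. **There is no time limit.** Sessions delivered after the day-10 scan count in the same way as earlier ones, although they cannot have affected that scan.

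At stake is how the per-protocol estimate will be read. It is assigned a role in judging efficacy, and the Discussion says that evidence of effect and adherence will inform whether a phase III trial is warranted. It is also run when deviations are many, which is when the filter removes most patients.

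**Working it through.** **1. The cut-off.** Five sessions minimum × 0.80 = 4. The stated minimum of four is arithmetically consistent with the five-session floor, so the threshold itself contains no error.

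**2. The time window.** Inputs: "Enrolled into the study within 96 hours of ICU admission" (Participants), endpoint at day 10 after enrolment (Outcomes), ICU sessions to day 28 after ICU admission (Study intervention).

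- Enrolled at ICU hour 0: the scan falls on ICU day 10, leaving 28 − 10 = 18 possible session days after it, or 18/28 = 64% of the days from enrolment to ICU day 28.
- Enrolled at 96 hours: the scan falls on ICU day 14, leaving 28 − 14 = 14 days, or 14/24 = 58%.

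So for a patient who stays in ICU, more than half of the possible session days lie after the primary measurement.

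**3. Can late sessions make a patient adherent?** This depends on the denominator of the 80%, which the article does not state.

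- *80% of the five-session minimum:* one session before the scan and four after it gives 5 ≥ 4, so the patient is in the set.
- *80% of one session per day from enrolment:* a patient with one session in the first ten days has missed nine. Inclusion needs D − 9 ≥ 0.8D, so D ≥ 45 days. The window is at most 28, so the patient is out.

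The example therefore holds on the first reading, which matches the stated minimum of four, and fails on the second.

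**4. Illustrative size of the selection.** Suppose there is no true effect, a fraction q of cyclists is retained as the upper part of a normally distributed variable, and that variable has correlation ρ with change in cross-sectional area. The retained cyclists then differ from all controls by

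shift = ρ × SD × φ(z₁₋q) / q.

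SD = 6 comes from the Sample size section. With the stated within-patient correlation of 0.5, the SD of a change score is 6 × √(2 − 2 × 0.5) = 6, so the same figure applies. The values of q and ρ are **not in the documents**; they are assumptions. For q = 0.8, φ/q = 0.280/0.8 = 0.350, and at ρ = 0.3 the shift is 0.3 × 6 × 0.350 = 0.63.

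| Cyclists excluded | ρ = 0.1 | ρ = 0.3 | ρ = 0.5 |
|---|---|---|---|
| 20% | 0.21 | 0.63 | 1.05 |
| 30% | 0.30 | 0.89 | 1.49 |
| 40% | 0.39 | 1.16 | 1.93 |

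Against the 2.9-point target, the range runs from 0.21/2.9 = 7% to 1.93/2.9 = 67%.

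**5. False-positive rate.** This was simulated under no effect with 27 completers per arm (the Sample size figure) before filtering the cycling arm, a two-sided t-test at 0.05, and 4,000 runs per setting.

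| Cyclists excluded | ρ = 0 | ρ = 0.3 | ρ = 0.5 |
|---|---|---|---|
| 20% | 4.5% | 6.4% | 10.0% |
| 40% | 5.4% | 8.7% | 17.1% |

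**The case against.** **The stakes are limited.** Intention-to-treat is primary, and the per-protocol analysis is additional and conditional. This stands: a reader might infer that the trial's main conclusion is compromised, and the documents do not support that. It could also be said that the control rule and exposure window belong in an analysis plan that is not shown. That answers an omission, but the article states an inclusion rule, and the rule as stated has these consequences.

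**The direction is not fixed.** A reader might infer that the rule necessarily favours cycling. Sessions end at hospital discharge, so quick recoverers may also fall short of four. The long window lets patients who stabilise late qualify, which weakens selection on severity. Crediting post-scan sessions would dilute a real day-10 effect. Patients who die before day 10 have no day-10 scan in either arm, so the one-sided selection operates mainly among survivors. All of this stands; a bias towards cycling is probable, not certain.

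**Excluding every control is a strained reading.** Taken literally, the session requirement would empty the usual-care arm. The workable reading is that it applies to cyclists, while controls adhere by not cycling. That is fair, but it leaves the comparison filtered on one side.

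**The magnitude is hypothetical.** The formula assumes clean truncation on one variable. Sessions may also be missed through refusal, femoral access or the priority given to usual physiotherapy. Covariate adjustment is possible if groups differ greatly, and Box 2 lists severity-adjusted analyses, though neither is tied to the per-protocol set. This stands, so the figures can only illustrate.

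**Conclusion.** The point holds in limited form. As written, the per-protocol comparison sets cyclists selected on a post-randomisation marker of illness course and length of stay against controls with no equivalent filter. It can also count exposure that came after the outcome. The time-window defect follows from the text; the specific example of one session before and four after requires that 80% refer to the five-session minimum.

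Under no true effect, the spurious difference could be about 0.2 to 1.9 points against a 2.9-point target. That range rests on assumed exclusion fractions of 20–40% and correlations of 0.1–0.5. It shows that the selection could be trivial or could be a large part of the target; it does not estimate what this trial would produce. Only the conditional secondary analysis is affected.

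**What to change.** Change the Analysis wording in three places.

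1. **Exposure window.** For the day-10 outcome, count only sessions delivered before the day-10 scan. For later outcomes, count sessions before that assessment, since later sessions are real exposure there. State what the 80% is a percentage of.
2. **Label.** Call the per-protocol comparison descriptive, and remove the suggestion that it is evidence of efficacy.
3. **Supplementary analysis.** Add a complier-average (instrumental-variable) analysis with randomised arm as instrument and number of pre-scan sessions as exposure, in all randomised patients with the outcome observed or imputed. State its assumptions: allocation affects the outcome only through sessions (exclusion restriction), and the effect is linear in the number of sessions. A four-session threshold should not be the exposure, because it treats patients with one to three sessions as unexposed and so breaches the exclusion restriction.

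The cost is a wider interval for the complier-average estimate and a little more analysis work. No new visits or measurements are needed, provided the session data sheets carry dates. The article describes the sheets but does not say so, and this should be confirmed.

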The strengths of this study are the implementation of the in-bed cycling intervention as soon as feasible (including while patients are still mechanically ventilated), with clear commencement and stopping rules. Another strength of the study is the blinded assessment of muscle structure, strength and function assessments. Measurement of the effect of early in-bed cycling on quality of life up to six months post ICU-admission is another strength that will assist to demonstrate if potential gains made early during a period of critical illness correspond to lasting functional improvements. It is expected that this study will also provide insights regarding the feasibility of the in-bed cycling intervention with patients with critical illness from the rates of compliance and completion of the in-bed cycling exercise intervention. The acceptability of in-bed cycling intervention from the perspective of patients with critical illness will be sought through a questionnaire and provide new information to inform potential implementation strategies for this intervention. A potential limitation of the study may be difficulty completing functional assessment measures at ICU discharge and at 1 week post-ICU discharge with patients who are either profoundly weak or present with an acute cognitive dysfunction. Further, usual care physiotherapy interventions will be delivered by treating teams independent of the study and prioritised over in-bed cycling. The frequency, intensity, type and duration of all usual care physiotherapy interventions are not being prospectively recorded as part of the trial outcomes. As the study design is an RCT, it is anticipated that the usual care physiotherapy will be similar across groups. Also this study is being conducted at a single centre and therefore results may need to be interpreted with caution.

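### Generalised linear mixed models are the only method named for time-to-milestone outcomes and the 6 min walk test, with no provision for death, non-achievement or inability

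*Protocol article*

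**What the plan says.** The Analysis section of the protocol article pairs descriptive statistics with one model family, generalised linear mixed models, which "will be used to examine the effect of group allocation (intervention vs usual care) on the primary and secondary outcomes". No other inferential method is named.

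Table 2 (Outcomes) lists among the secondary outcomes "Time to achieve functional milestones: sit out of bed, time to stand, mobilise with assistance and mobilise independently", and the 6 min walk test, described as "Submaximal endurance test of distance walked by a patient in 6 min". In Table 3, milestones are followed from baseline to one week after ICU discharge, or to hospital discharge if that comes sooner. The walk test is done once, at that last visit.

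Two missing-data rules are given: "Statistical analysis of available data will be used for the primary analysis when data are completely missing", and "Multiple imputation will be conducted if more than 20% of outcome data are missing".

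The protocol expects patients without a result. Sample size allows for dropout of up to 20%, with deaths in hospital counted in it. The Discussion foresees difficulty in completing functional tests "with patients who are either profoundly weak or present with an acute cognitive dysfunction".

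**The concern.** Time to a milestone is a censored time. Some patients will not have reached it when observation ends, and death rules it out. A mixed model for the number of days needs a number for each patient, and these patients have none. The walk test has the same problem: a patient too weak to walk has no distance unless the plan assigns one.

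Whether a value exists therefore depends on the outcome itself. If cycling helps, more slow or frail patients become measurable in that arm, which pulls its observed average towards the control arm. If survival differs between arms, the distortion can go either way.

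This matters because better functional outcome belongs to the trial's second objective, and the Discussion says the secondary outcomes will help to size future studies. A distorted estimate would carry over into that planning.

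**Working it through.** **Inputs from the protocol.** 68 patients, 34 per group, dropout up to 20% including deaths in hospital. 0.20 × 68 = 13.6, about 14 patients; 34 × 0.80 = 27.2, which matches the stated 27 or so completers per group. The sample size concerns muscle cross-sectional area and says nothing about milestones. No milestone rate, walk distance or proportion unable to walk is given, so everything below is assumed and illustrative.

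**Illustration 1: lognormal times, random exit.** Medians 10 (control) and 8.5 days (cycling), log-scale SD 0.7, exponential exit with the same distribution in both arms, 4 million simulated patients per arm. True mean difference: (8.5 − 10) × exp(0.7²/2) = −1.5 × 1.278 = −1.92 days. Shortfall = 1 − (achievers-only difference ÷ true difference), computed before rounding.

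| Median exit (days) | No observed time, control / cycling | Achievers-only difference (days) | Shortfall |
|---|---|---|---|
| 60 | 13% / 11% | −1.64 | 14% |
| 40 | 19% / 16% | −1.54 | 20% |
| 20 | 33% / 29% | −1.32 | 31% |
| 12 | 46% / 42% | −1.10 | 42% |
| 8 | 58% / 53% | −0.93 | 51% |

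Only the first two rows lie below the 20% level at which the protocol turns to imputation.

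**Illustration 2: exponential times, fixed end of observation.** 34 per arm, control median 8 days, hazard ratio 1.5, equal mortality of 10% or 20%, observation to day 21 or 28. Between 8% and 17% of patients have no observed time.

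- Untruncated means: 8/ln 2 = 11.54 and 11.54/1.5 = 7.69 days, a difference of −3.85.
- Achievers-only difference: −1.2 to −1.8 days. Part of this gap is the long tail that no analysis would observe, so power is the fairer measure.
- Power: 11% to 15% for a t-test on log time in achievers, against 28% to 32% for a log-rank test that keeps everyone, with deaths held as not reached.
- With no difference between arms, the achievers-only test rejects in 4% to 5% of trials. With equal mortality, then, the harm is attenuation and lost power, not false positives.

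**Illustration 3: walk test.** Latent distance normal with means 50 and 90 m and SD 150 m; values at or below 0 mean unable to walk (37% and 27%).

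- Inability scored 0: mean = μΦ(μ/σ) + σφ(μ/σ), giving 50 × 0.631 + 150 × 0.377 = 88 m and 90 × 0.726 + 150 × 0.333 = 115 m, a difference of 27 m.
- Walkers only: 88/0.631 = 140 m and 115/0.726 = 159 m, a difference of 19 m.

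If inability counts as missing, these proportions exceed 20% and imputation would apply. The example shows direction; it does not forecast the planned analysis.

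**The case against.** The strongest reply is that nowhere does the protocol say these patients are dropped. The available-data sentence speaks of the primary analysis and sits in the paragraph on ultrasound scans. It reaches secondary outcomes only if primary analysis there means the intention-to-treat analysis, as it does earlier in the section. A generalised linear mixed model can also be a discrete-time binomial model on the Table 3 visits, which would keep and censor non-achievers. Participants discharged home are asked to return for outstanding measures. Censoring rules and scoring of inability are often left to an analysis plan, and one may exist. All of this stands, so omission is a possibility and not a stated step.

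Some further inferences are also unsupported:

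- Imputation would not simply give untested patients average values. It can draw on severity scores, serial muscle size and the ICU-discharge tests. What remains is that a walk distance after death does not exist, and that an imputed milestone time need not respect the follow-up already observed without it.
- Lack of a baseline walk or strength test is no contradiction. The text says the models can adjust for baseline status, which is a capability and not a commitment for every outcome.
- The MRC sum score and FSS-ICU are ordinal scales on which weak patients may still be scored.

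The reply does not remove the core. The method printed for censored times is a general one, nothing points to a discrete-time form, and neither missing-data rule suits a patient who died or could not perform the test.

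**Conclusion.** The point holds for the time-to-milestone outcomes and the 6 min walk test. The protocol assigns them a model family without providing for death, non-achievement or inability, while expecting all three. Up to 20% missing, such patients could be left out; above that, they would receive imputed values.

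The size cannot be fixed from the documents. Under the assumed lognormal times the shortfall is about 14% to 20% when 11% to 19% of patients have no observed time. It is larger with heavier loss, and can also be larger where a fixed end of observation cuts off the slow patients. These figures assume the same exit pattern or mortality in both arms; unequal mortality could shift the result in either direction.

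A reader might infer that the plan definitely excludes these patients, or that the main result is at risk. Neither follows. Exclusion is not stated, and the primary outcome, muscle cross-sectional area, is unaffected. The trial also says it may not be powered for all secondary outcomes. The change is nevertheless worth making, because it is cheap and these outcomes will inform later trials.

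**What to change.** **Milestones.** Analyse from randomisation with a time-to-event method: cumulative incidence curves with a cause-specific Cox or Fine-Gray model, or a discrete-time model on the scheduled visits. Treat death as a competing event, censor patients who have not reached the milestone at the end of observation, and state when that is.

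**6 min walk test.** Record why each test was not done. Score physical inability to walk as 0 m and compare the arms with a rank-based method. Report deaths separately. Treat tests missed for other reasons, including cognitive dysfunction, as missing.

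**Cost.** Some analysis wording and one reason-not-done field; no extra patients or visits. The results are less directly read in days or metres, so also report the achievers-only and walkers-only summaries, labelled as descriptive.
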